## Methods

### Aims and hypothesis

The overall aim of this project is to develop TapTalk – a smartphone test that detects risk of AD pathology and is usable, reliable and validated against blood-biomarkers of AD pathology, cognitive screening tests and clinical diagnosis. We will address the hypothesis: “*Hand-speech movement patterns will detect the risk of Alzheimer’s disease pathology in research and clinical cohorts of older adults*”, where research cohorts have normal cognition and no cognitive symptoms, and clinical cohorts have cognitive symptoms.

Our interdisciplinary team of clinician-researchers (Neurologist, Speech Pathologist, Physiotherapist, General Medicine Physicians, General Practitioner (GP), Neuropsychologist), computer scientists (specialising in Artificial Intelligence and machine learning), data analysts, and neuroscience researchers (specialising in ageing, dementia and blood-based biomarkers) will work together to address the hypothesis through three studies, with each study addressing one of the following aims:

**Aim 1.** Determine which combinations of hand-speech movement data most accurately predict preclinical AD.**Aim 2.** Develop smartphone capability for TapTalk and determine usability, reliability and validity.**Aim 3.** Prospectively validate TapTalk in people who have cognitive symptoms against gold-standard consensus clinical diagnoses of MCI and AD dementia, with comparison to other screening tools commonly used in clinical settings.

### AIM 1

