### Setting

Most participants will complete the hand and speech-like movement tests online remotely either at home, or another setting of their choosing, using their own laptop or desktop computer. If they cannot access a computer with a computer camera and microphone, they may attend one of the University of Tasmania research sites to complete the tests on a university laptop. The TAS Test software is an online ‘self-test’ program that guides the participant through a series of screens to collect a range of motor, cognitive and speech tests [38]. It has already successfully collected finger tapping and hand movement data online (as well as various cognitive tests) from ∼1,800 ISLAND Project participants at home and ∼400 participants at University of Tasmania research settings [19, 42]. For the TapTalk project, the TAS Test software will be adapted to collect new finger tapping test data and include an online version of DDK tasks to collect speech-like data.

The full protocol of TAS Test is described in Alty et al.; [38] in brief, when participants log into the TAS Test software, and provide consent online to take part, they are shown an introductory video and general instruction screens. Next, they are asked for permission for the software to switch on their computer camera and microphone. Each individual test (e.g., ‘right hand finger tapping at comfortable pace’ test) within TAS Test has an ‘instruction’ screen followed by a ‘recording’ screen, followed by a “*well done, you have completed the test*” message. To move to the next screen, the participant clicks the ‘next’ button which means the tests are self-paced and participants can take a break at any time. They are shown their progress through TAS Test by green dots on a ‘progress bar’ at the top of the screen; see Fig. 2.

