### Hand movement data collection

For each of the hand movement tests, the participant is asked to hold their hands up about 50 cm in front of the computer camera and adjust their position until they can see an image of their hands on the screen fitting completely inside green ‘data collection’ boxes. This careful positioning of the hands at the start of each test assures that the camera can record the movement patterns accurately. Computer-user interface technologies are embedded into the TAS Test software that respond to the positioning of the participant’s hands and give them on screen text prompts (e.g., “your right hand is correctly positioned”, “move your left hand closer to the screen”, or “well done your hands are in the correct position”) to prompt adjustments in the hand positioning as required. These technologies have been purposefully included to allow TAS Test to collect robust data at home, or any remote setting, without any in-person researcher assistance being required [42].

The hand movement tests comprise tests of repetitive finger tapping (index finger tapping against thumb) tests, and of repetitive ‘sequential’ finger tapping (index, middle then ring finger each in turn tapping against the thumb, then index, middle, ring etc.). The sequential finger tapping tests are a commonly used clinical test of motor function chosen in this study for direct comparison with the Sequential Motion Rate analysis in the DDK test. Each test is about 10 s duration and completed in a fixed order as follows: (i) at a comfortable pace: right hand finger tapping, left hand finger tapping, right hand sequential finger tapping, left hand sequential finger tapping; (ii) at a maximal pace ‘as big and fast as you can’: right hand finger tapping, left hand finger tapping, right hand sequential finger tapping, left hand sequential finger tapping; (iii) at maximal pace: both hands finger tapping together in phase, both hands finger tapping together out of phase, both hands finger tapping together in phase with a cognitive task, both hands finger tapping together out of phase with a cognitive task.

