‘In phase’ means that both hands move simultaneously through the finger tapping cycle, whereas ‘out of phase’ means that each hand moves through the finger tapping cycle in the opposite direction to the other hand (i.e., 180 degrees out of phase so one hand has the finger and thumb opposed while the other hand has the finger and thumb spread apart). The cognitive task will be counting backwards aloud from 100 and constitutes a ‘dual motor-cognitive test’ when performed at the same time as finger tapping [53, 54]. Each hand will therefore be tested separately, and together, at a comfortable pace and at maximal pace, allowing for a number of finger-tapping measures to be calculated including, but not limited to, frequency, rhythm, inaccuracies (i.e. the wrong digit tapped on the sequential tests), ‘motor reserve’, calculated as a ratio (the maximal pace parameter divided by comfortable pace parameters), bimanual ‘motor cost’, calculated as the finger tapping parameters of one hand divided by the finger tapping parameters of same hand when both hands tapped together and the ‘dual cognitive-motor cost’, calculated as the finger tapping parameters divided by the finger tapping parameters during the counting backwards aloud from 100 task.

We will shorten this finger tapping protocol to around three to five tasks, aiming for a test duration of 2 to 3 min, in the smartphone version of TapTalk that will be used in Aim 2 and Aim 3. The choice of which tasks will comprise the shortened protocol will be based on the findings from Aim 1. We have purposefully kept a wide array of tests in Study 1 to clarify which tests combine best together, and with the DDK data, to best discriminate biomarker-defined AD pathology.

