### Speech-like data collection

It is unclear which tests are most sensitive in preclinical AD. We will replicate the clinical DDK [23, 27] test but under both comfortable and maximal speed conditions. A participant will be instructed to say “pa, p.a., pa…” repetitively for 10 s at a comfortable pace, then the participant will be instructed similarly for “ta, ta, ta…”, “ka, ka, ka…” and “pa-ta-ka, pa-ta-ka…” all at a comfortable pace. After this, they will be instructed, to repeat each test in turn but this time at maximal pace. These deceptively simple tests assess the motor function of the lips (p.a.), tongue (ta) and palate (ka) respectively, allowing us to calculate the speed, rhythm, accuracy, and motor reserve (‘maximal pace’ measures divided by ‘comfortable pace’ measures) for each syllable.

Similar to the format of the hand movement tests, there will be an ‘instruction’ screen and a ‘recording’ screen followed by a “well done” screen. The difference compared to the hand movement tests, in terms of the software, is that the recording screen does not show a video image of the participant as they perform the task; see Fig. 3. At the end of the protocol, the participant will be asked to complete a questionnaire on their experience of the tests and suggestions for improvement.

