### Extracting hand-speech movement data

We will use deep neural networks and other machine learning methods to develop and train two computer programs that will automatically detect, respectively, hand key points (e.g. finger and thumb tips) in the video data [43], and syllable features in audio recording (Fig. 1). A series of movement features will be extracted in a fixed window period, by (1) experts in hand movement (JA, KL, [name]) and speech-like movements (LG), and (2) deep-learning approach applied directly on processed video data, to analyse their associations with biomarker-defined measures of AD pathology. The processed video data can be the hand-only cropped video or displacement (between fingertip and thumb-tip) over time data extracted from the raw video. Thus, two approaches, expert guided and AI-based ‘deep-learning’, will extract discriminative hand-speech movement features as input data for the multivariable model. The main outcome will be a validated personal computer (laptop and desktop) version of the TapTalk that discriminates preclinical AD from normal ageing in cognitively healthy adults ≥ 50 years old with defined sensitivity and specificity.

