#### Statistical analysis

The data from participants who complete TapTalk on two or more occasions over an 18-month period, and CANTAB on two occasions (2021 and 2023) will be included in the analysis. De-identified ISLAND Project participants will be classified as cognitively ‘stable’ or ‘declining’ using longitudinal CANTAB cognitive scores. TapTalk scores will be calculated using algorithms developed in Study 1. Logistic regression will be used to estimate the odds of a participant being confirmed as ‘declining’ at time T_2_ (24 months) conditioned on TapTalk score at time T_1_ (12 months). The overall outcome of Study 2 will be a smartphone app, TapTalk, that is usable, reliable and validated against established online CANTAB cognitive tests.

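### TapTalk is presented as a smartphone test validated against blood biomarkers, but the only biomarker analysis stated is of the longer computer version

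*Protocol article*

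**What the plan says.** **The claim.** Under Aims and hypothesis, the project's product is "a smartphone test that detects risk of AD pathology and is usable, reliable and validated against blood-biomarkers of AD pathology", and also validated against cognitive screening and clinical diagnosis. The Discussion paragraph of the abstract and the opening of the main Discussion likewise describe a smartphone tool that estimates the risk of preclinical AD.

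**The biomarker study.** In Aim 1 (Setting), most participants do the tests "using their own laptop or desktop computer". The stated outcome is "a validated personal computer (laptop and desktop) version of the TapTalk that discriminates preclinical AD from normal ageing". Statistical analysis for Aim 1 splits 500 people into 350 for development and 150 for validation, and takes the model with the highest AUC as the TapTalk algorithm.

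**The phone version.** Hand movement data collection says "We will shorten this finger tapping protocol to around three to five tasks", chosen from the Aim 1 findings. The Aim 2 Design section applies the same three-to-five range to hand and speech-like movements together, and allows further refinement after Studies 2.1 and 2.2. For Study 2.3, "TapTalk scores will be calculated using algorithms developed in Study 1".

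**The concern.** The device, the number of tasks and possibly the fitted model all change between the biomarker study and the phone studies. No stated analysis carries the biomarker result across those changes.

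The phone studies' other references cannot stand in for a biomarker on the protocol's own reasoning. The abstract says cognitive tests are normal in preclinical AD, and the Background says the MoCA lacks sensitivity until the MCI stage. Study 3 enrols only people with cognitive symptoms, so it cannot measure accuracy in the preclinical stage.

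At stake is whether a sensitivity and specificity for preclinical AD, measured on a computer with a longer battery, come to be read as those of the phone app.

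**Working it through.** **1. Reference standard by study**

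| Study | Device | Compared with |
|---|---|---|
| Aim 1 | Laptop or desktop | Blood biomarker (p-tau 181 or a combination) |
| 2.1 | Smartphone | Polhemus sensors, high-quality microphone |
| 2.2 | Smartphone | The same person's repeat tests; usability questionnaire |
| 2.3 | Smartphone | CANTAB, stable or declining |
| 3 | Smartphone | Consensus clinical diagnosis, alongside MoCA or RUDAS |

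No row pairs a smartphone with a blood biomarker.

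**2. Size of the Aim 1 battery**

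- Hand tests ("Each test is about 10 s duration and completed in a fixed order as follows"): 4 comfortable + 4 maximal + 4 two-handed = 12.
- Speech-like tests (four at a comfortable pace, then "After this, they will be instructed, to repeat each test in turn but this time at maximal pace"): 4 + 4 = 8.
- Total: 12 + 8 = 20.

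**3. What the phone keeps**

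- Under the Aim 2 Design section: 3 to 5 of 20 are kept, so 15 to 17 are dropped.
- Under Hand movement data collection: 3 to 5 of the 12 hand tasks are kept, so 7 to 9 are dropped. The number of speech tasks is not given. If all 8 stayed, 11 to 13 of 20 would remain.

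The two sections do not agree on what the three-to-five range covers.

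**4. Can the Aim 1 model be scored on the phone?**

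Only if every feature in it comes from a retained task. Each motor-reserve ratio needs a comfortable and a maximal recording of the same task. Aim 1 has 4 hand + 4 speech = 8 such pairs, and five tasks can supply at most two. The highest-AUC rule does not require the chosen model to fit within that.

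**5. The plan's own case numbers**

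Sample size justification for Aim 1 takes 17% biomarker-positive: 0.17 × 350 = 59.5 (stated 60) and 0.17 × 150 = 25.5 (stated 25). These reproduce, and both describe the computer version.

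**6. Precision of a phone-versus-biomarker comparison**

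The Hanley–McNeil variance for m positives and n negatives is

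Var = [A(1−A) + (m−1)(Q1−A²) + (n−1)(Q2−A²)] / (mn), with Q1 = A/(2−A) and Q2 = 2A²/(1+A).

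At an assumed A = 0.80: Q1−A² = 0.0267 and Q2−A² = 0.0711. With 500 people at 17%, m = 85 and n = 415:

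Var = [0.16 + 84 × 0.0267 + 414 × 0.0711] / 35,275 = 0.00090, so SE = 0.030 and the 95% half-width is 1.96 × 0.030 = 0.06.

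| People with both results | Positives / negatives | 95% half-width, AUC 0.80 |
|---|---|---|
| 200 | 34 / 166 | 0.09 |
| 500 | 85 / 415 | 0.06 |
| 1,000 | 170 / 830 | 0.04 |
| Aim 1 hold-out (computer), for reference | 25 / 125 | 0.11 |

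Study 2.2 alone (50 to 100 people, 8.5 to 17 positives) gives about 0.19 to 0.13. That is too wide for validation, so its use is to compare computer and phone scores.

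**The case against.** The strongest reply is that Aim 1 exists to find the best combination of tasks, and that the phone tasks are picked from its results. The type of penalty is left to cross-validation, and Study 2.3 refers to algorithms in the plural. A sparse model, or one restricted to the retained tasks, could therefore be scored on the phone. This stands: a reader might infer that the Aim 1 algorithm cannot be scored from the phone tasks at all, and the protocol does not establish that. What remains is that nothing ensures the chosen model fits the retained tasks, and no held-out accuracy is stated for a shortened version.

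A reader might also infer that the project's main claim goes untested. That is too strong. The hypothesis concerns hand-speech movement patterns. It is tested against the biomarker on computers with 150 held-out participants, and the cognitive and clinical parts of the aim are tested on phones.

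The study-level outcomes are, moreover, labelled with care: Aim 1 names the personal computer version, Study 2 names CANTAB, and Study 3 names clinical diagnosis. This too stands; the unsupported wording sits in the overall aim and the general statements.

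Study 2.1 may yield a correction factor for phones. It is calibrated to sensors and a microphone, however, not to the computer test or the biomarker.

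Details of a refit could sit in an analysis plan. The mismatch between the overall aim and the listed comparisons is in the protocol itself.

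**Conclusion.** The concern holds in limited form. The overall aim promises blood-biomarker validation of a smartphone test, and no stated analysis relates a smartphone score to a blood biomarker. The accuracy of a full-battery computer model in the 150 held-out participants is not the accuracy of a shortened phone version.

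The reduction is 15 to 17 of 20 recordings under the Aim 2 Design section. Under Hand movement data collection it is 7 to 9 of the 12 hand recordings, with the speech cut not stated.

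The precision figures rest on three assumptions: an AUC of 0.80, the protocol's 17% prevalence carrying over to Study 2.3, and an overlap of 200 to 1,000 people. The protocol reports more than 1,500 people with blood samples and about 3,000 with 2021 CANTAB results, but not how many have both and would also complete TapTalk.

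The plan should be corrected before results are reported, either by adding the comparison or by narrowing the claim.

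**What to change.** 1. Within the 350 development participants, select the smartphone tasks, then refit and lock an algorithm that uses only those tasks. Report its sensitivity and specificity in the 150 held-out participants, labelled as computer-collected. Reconcile the two statements of what the three-to-five range covers.
2. In Study 2.2, whose participants all took part in Study 1, report agreement between each person's computer and phone scores.
3. In Study 2.3 participants who were not used for development and have an ISLAND p-tau 181 result, report the AUC, sensitivity and specificity of the locked phone score at T0. State the interval between blood sample and test, since blood is collected every second year.
4. If step 3 is not done, restate the overall aim so that blood-biomarker validation applies to the personal computer version only, and align the abstract and Discussion.

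**Cost.** Steps 1 and 2 are extra analyses of data the plan already intends to collect. Step 3 may also need assays: samples have been taken, but the protocol describes the measurements in the future tense and notes that access to the analytic equipment is costly. The reduced algorithm's AUC may be lower than the full battery's. Step 4 costs nothing.

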#### Design

We will undertake a cross-sectional single site study. Overview of the methods is presented in Fig. 1.

**Fig. 1 Fig1:**
[figure not shown]
Cross-sectional study (n = 500) to identify hand-speech motor biomarker classifier

#### Participants

We aimed to recruit at least 500 eligible participants (see below for inclusion and exclusion criteria) with normal cognition from the ISLAND Project. As of March 2024, we have recruited 1382 adults, with mean (SD) age 66.20 (7.65) years, range 50–92 years, and 72.07% female. The ISLAND project was launched in October 2019 at the University of Tasmania as a 10-year prospective cohort study of Tasmanians ≥ 50 years old with nested interventions to reduce dementia risk [45, 46]. To date, > 14,000 people have been recruited to the ISLAND Project; 8,500 research participants (mean age 63 years) have provided detailed demographic and health data, 3,000 have completed the online validated Cambridge Neuropsychological Test Automated Battery (CANTAB) cognitive tests [47], 1,800 have completed online motor-cognitive tests (TAS Test) [38] and more than 1,500 have provided blood samples. Paired Associates Learning (PAL) scores distinguish between older adults with MCI and those who are cognitively healthy with a sensitivity/specificity of 0.83/0.82 [48]. The online ISLAND Project surveys are repeated annually with cognitive performance and blood-based biomarkers collected every second year.

##### Inclusion criteria

Adults ≥ 50 years old who are (i) participants in the ISLAND Project [45] (ii) have provided a blood sample for analysis of blood-based biomarkers, (iii) have *normal* cognition defined as not ≥ 2 SD above the mean total errors (adjusted for age) on the CANTAB PAL tests, and (iv) have no history of persistent cognitive symptoms reported on ISLAND Project questionnaires (all participants are asked each year: *Have you noticed a substantial change in your memory and mental function in recent years*? [YES/NO], *Have you been told by a doctor that you have dementia?* [YES/NO], *Have you been told by your doctor that you have a memory impairment but they were uncertain if you have dementia?* [YES/NO], *Have you discussed concerns about your memory and mental function with your doctor or other health professional?* [YES/NO]).

##### Exclusion criterion

Adults < 50 years old or those who have impaired cognition, defined by a diagnosis of dementia or MCI or a validated cut-off score ≥ 2 SD above the mean total errors, adjusted for age, on the CANTAB PAL tests or reporting ‘YES’ on any of the ISLAND annual questions ‘*Have you noticed a substantial change in your memory and mental function in recent years?*’ *Have you been told by a doctor that you have dementia?* [YES/NO], *Have you been told by your doctor that you have a memory impairment, but they were uncertain if you have dementia?* [YES/NO], *Have you discussed concerns about your memory and mental function with your doctor or other health professional?* [YES/NO]).

As part of the ISLAND Project, we will measure blood levels of a range of proteins known to be associated with AD pathology, including p-tau 181 [45, 49], glial fibrillary acidic protein (GFAP) and neurofilament light (NFL) [45, 49]. Although minimally invasive, the practicalities and cost of accessing the specialist analytic equipment limit wide accessibility. We will use ultrasensitive Simoa® immunoassays measured using the SR-X™ platform from Quanterix™ for blood biomarker analysis in a dedicated biobank with − 80 °C freezers for sample storage.

Based on the latest scientific literature, and recognising emerging work around variability we will either define cut-off ranges for biomarker levels that are indicative of risk for AD dementia or examine associations across continuous measures [50]. This ‘AD biomarker’ in the TapTalk project is likely to be based on one or more blood tests for validated proteins such as p-tau181, GFAP and NFL [12, 51, 52]. The field of AD blood biomarkers is developing rapidly [14], and we anticipate further pathological markers will become available during the life of this project; we will assess such new markers in the samples collected from study participants.

### Setting

Most participants will complete the hand and speech-like movement tests online remotely either at home, or another setting of their choosing, using their own laptop or desktop computer. If they cannot access a computer with a computer camera and microphone, they may attend one of the University of Tasmania research sites to complete the tests on a university laptop. The TAS Test software is an online ‘self-test’ program that guides the participant through a series of screens to collect a range of motor, cognitive and speech tests [38]. It has already successfully collected finger tapping and hand movement data online (as well as various cognitive tests) from ∼1,800 ISLAND Project participants at home and ∼400 participants at University of Tasmania research settings [19, 42]. For the TapTalk project, the TAS Test software will be adapted to collect new finger tapping test data and include an online version of DDK tasks to collect speech-like data.

The full protocol of TAS Test is described in Alty et al.; [38] in brief, when participants log into the TAS Test software, and provide consent online to take part, they are shown an introductory video and general instruction screens. Next, they are asked for permission for the software to switch on their computer camera and microphone. Each individual test (e.g., ‘right hand finger tapping at comfortable pace’ test) within TAS Test has an ‘instruction’ screen followed by a ‘recording’ screen, followed by a “*well done, you have completed the test*” message. To move to the next screen, the participant clicks the ‘next’ button which means the tests are self-paced and participants can take a break at any time. They are shown their progress through TAS Test by green dots on a ‘progress bar’ at the top of the screen; see Fig. 2.

